#### EEG substudy

All raw EEG data will be pre-processed with BrainVision Analyzer (Version 2.0, Brain Products GmbH, Gilching, Germany) according to current standards including ICA-based correction of eye-movement artefacts, artefact rejection and application of band-pass filtering (see e.g., [94–96]). Event-related potentials (ERPs) will be computed for each stimulus type in the three experiments (IAT, GNG, SST). Epochs from 500 ms (pre-stimulus) to 1500 ms (post-stimulus) will be averaged separately for each stimulus type and measurement point (T2 and T3). ERPs will subsequently be statistically compared for overall amplitude (i.e., global field power, GFP) and topography. For each ERP, GFP [97] will be calculated as the standard deviation across electrodes, thus measuring momentary global signal strength regardless of topographic modulations. GFP values for each point in time will be extracted and compared (T2 vs. T3) with nonparametric randomization tests, which simultaneously control for multiple comparisons. The analyses will be conducted using the Ragu software [98, 99].

To inspect for topographic differences between ERPs measured before and after the training, a topographic analysis of variance (TANOVA) [100] will be computed in Ragu. Here, dissimilarities of electric field topographies are identified with a nonparametric randomization test. A significant finding in the TANOVA indicates that activation in underlying brain structures vary in relation to the factor under investigation. Significant TANOVA results will be further explored with the standardized low-resolution electromagnetic tomography (sLORETA) source analysis method [101]) to determine which brain regions vary in activation in relation to stimulus type and/or measurement time (T2 vs. T3).

Based on prior findings, our ERP analyses will focus on the timeframe from about 150 to about 850 ms. Exact timeframes will be defined based on components as visible in GFP-curves or by microstate analyses [102, 103]. Following earlier research, care will be taken to include the N2 and P3 components in case of the GNG [25, 26] and the N2, P3, N4 and LPP components in case of the IAT (e.g., [104–106]).

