### Research questions

Based on prior research, the following five research questions are examined:Does the alcohol-specific inhibition training (Alc-IT, compared to the control intervention) reduce PDA and HDD and/or extend the time to first drink (TFD) at 3-months’ follow-up (primary outcomes)?What is the effect of the Alc-IT on behavioral experimental parameters?Does Alc-IT decrease positive implicit associations compared to the control training?Does Alc-IT enhance response inhibition compared to the control training?Are the neurophysiological correlates of alcohol-specific inhibition and implicit associations towards alcohol changed by Alc-IT?Does endogenous cortisol moderate the effect of the Alc-IT?In addition, explorative questions investigate whether the effects of the training on outcomes are mediated by AUD-related psychological constructs, such as alcohol-related self-efficacy, craving or motivation

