#### T2: Pre-training assessment

Prior to the training, all subjects will undergo an assessment including a series of questionnaires as well as experimental tests measuring implicit associations towards alcohol (IAT) and inhibitory control (GNG, SST). This will take place at the end of the third treatment week. A total of 60 patients (for the EEG substudy) will additionally be assessed with multi-channel EEG while completing the experimental tasks. As the intense confrontation with alcohol pictures may lead to tension and induce craving in patients with AUD, we will monitor our participants’ stress and craving on an 11-point Likert scale (0 = not at all, 10 = very strong) immediately before and after the assessment. In the case of significant stress or craving levels, the medical staff on duty will be contacted and informed.

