#### T3: Post-training assessment

One to 4 days after the last training session, patients will undergo the same assessment as in T2 (including questionnaires and experimental tasks). The 60 participants of the EEG substudy again participate in the EEG recording during the experimental tasks. Before and after the measurement, self-reported stress and craving will be assessed (see also T2).

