#### EEG substudy

As this involves more time-consuming measurements at T2 and T3, a two-level recruitment-process will be implemented: Inclusion and exclusion criteria for the substudy match those of the main study. However, recruitment of these participants will additionally depend on their mental capacity, age and gender balance, and their available time considering the clinic’s already demanding agenda. If eligible patients are interested in participating, additional information concerning EEG measurements will be provided, and an additional informed consent for this substudy will be signed. When 20 participants per training version are included in this substudy, the recruitment procedure will be stopped. Patients enrolled in the EEG substudy will receive a monetary compensation of 50 CHF per measurement.

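### The EEG tests are written as T2 versus T3 without training group, so as stated they cannot isolate an Alc-IT effect that the design itself could test

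*Protocol article*

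**What the plan says.** The question (Protocol article, Research questions) is about the effect of the training: "Are the neurophysiological correlates of alcohol-specific inhibition and implicit associations towards alcohol changed by Alc-IT".

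The analysis (Statistics, EEG substudy) is set out step by step:

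- ERPs are "averaged separately for each stimulus type and measurement point (T2 and T3").
- Amplitude: "GFP values for each point in time will be extracted and compared (T2 vs. T3) with nonparametric randomization tests".
- Topography: "To inspect for topographic differences between ERPs measured before and after the training, a topographic analysis of variance (TANOVA") is computed.
- Source analysis follows significant TANOVA results, to find "which brain regions vary in activation in relation to stimulus type and/or measurement time (T2 vs. T3").

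None of these steps mentions training group, Alc-IT or the control training.

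The data would allow a group comparison. Under Procedure for substudies, EEG substudy: "When 20 participants per training version are included in this substudy, the recruitment procedure will be stopped". The T2 section gives the total: "A total of 60 patients (for the EEG substudy) will additionally be assessed with multi-channel EEG while completing the experimental tasks". At T3, "patients will undergo the same assessment as in T2 (including questionnaires and experimental tasks"), and the EEG patients are recorded again.

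**The concern.** A before-after difference answers a causal question only if nothing else changes in the interval. Here several things change in every arm: patients see the same tasks a second time, they remain abstinent and in inpatient treatment, and they complete six training sessions over 2 weeks. The control training is itself an inhibition training. By Table 1 it contains 40 alcohol NoGo trials per session, so 6 × 40 = 240 over the course, against 6 × 80 = 480 in either Alc-IT version. The Discussion concedes that it might improve general inhibitory capacity. A T2-T3 change is therefore plausible without any effect specific to Alc-IT.

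The healthy participants cannot fill the gap. The Abstract and the Healthy controls section have them measured once. A bracket under Procedure for healthy controls mentions T2 and T3, but even on that reading they receive no training and are not randomised. Only the control-training arm can separate the common change from the specific one. Without it, the neurophysiological question would be answered by an uncontrolled contrast inside a randomised trial.

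**Working it through.** **Step 1. Factors named, side by side.**

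| Analysis | Measurement time | Training group | Other |
|---|---|---|---|
| PDA, HDD (Main study) | T1, T5 | named | none |
| Experimental test parameters (Main study) | T2, T3 | named | time of day |
| GFP (EEG substudy) | T2, T3 | not named | ERPs formed by stimulus type |
| TANOVA (EEG substudy) | before, after | not named | none stated |
| sLORETA (EEG substudy) | T2, T3 | not named | stimulus type |

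Where the Main study subsection describes its ANOVAs, it lists the group factor. The EEG subsection lists its contrasts too, and group is not among them.

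**Step 2. What each contrast estimates.** Let the mean T3 − T2 change in arm g be c + δ_g, where c is common to all arms and δ_g is specific to the version. With 20 patients per arm:

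- T2 versus T3 over all 60 patients estimates c + (δ_50/50 + δ_75/25 + δ_control)/3.
- T2 versus T3 within one arm estimates c + δ_g.
- Group by time tests whether the δ_g differ; c cancels.

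Only the last addresses the question. Pooling also dilutes a real effect: with c = 0, δ_control = 0 and both Alc-IT versions at δ, the pooled mean change is 2δ/3.

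**Step 3. Sample size.** The protocol gives no power figure for EEG. Its size is 3 × 20 = 60, consistent between sections.

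**Step 4. Illustration with no version-specific effect.** Assumption: a common shift d in SD units of the change score. The documents give no EEG retest effect, so a range is shown. For a two-sided paired t test at α = 0.05, the noncentrality is d√n with n − 1 df.

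| d | n = 60 (pooled) | n = 20 (one arm) |
|---|---|---|
| 0.2 | 33.2% | 13.6% |
| 0.3 | 62.8% | 24.7% |
| 0.4 | 86.2% | 39.7% |
| 0.5 | 96.8% | 56.5% |

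A group by time test (ANOVA of change scores, 3 × 20, 20,000 simulated trials each at d = 0, 0.3 and 0.5) rejects in 5.2%, 4.8% and 5.1%.

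Testing each arm separately does not help. With identical true change, the chance that the three arms disagree on significance is 1 − p³ − (1 − p)³. For d = 0.3 this is 1 − 0.247³ − 0.753³ = 0.56; for d = 0.4 it is 1 − 0.397³ − 0.603³ = 0.72.

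**Step 5. Power of the right test.** The Power calculation section uses f = 0.15 and r = 0.4 for the experimental parameters. As a check on the formula, λ = N f² × 2/(1 − r) with 6 groups (df 5, N − 6) needs N = 177 for 80% power; the next multiple of 6 is the stated 180. Borrowing the same values for EEG with 3 groups: λ = 60 × 0.0225 × 2/0.6 = 4.5 on (2, 57) df, power about 44%. For 80% power, f on the change score must be about 0.41; the borrowed values correspond to 0.15 × √(2/0.6) = 0.27.

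**The case against.** The best defence is that this is a condensed article, and its list of EEG contrasts need not be complete. The Discussion promises a comparison of patients' neurophysiological data with healthy controls, and the Study aim promises to relate EEG effects to clinical outcomes; the EEG statistics describe neither. The cortisol statistics give only the assay. The TANOVA text speaks generically of the factor under investigation, which does not exclude group. Recruiting equal numbers per version makes little sense unless versions are to be compared.

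Much of this stands. A reader might infer that the investigators chose to ignore the randomisation, or that the substudy cannot answer its question. The documents support neither: the recruitment rule points to an intended group comparison, and the design allows one. A reader might also infer that the arms will be pooled and any T2-T3 change reported as caused by Alc-IT. The text does not say so. Nor are the percentages above rejection rates of the planned procedure: they come from a single-endpoint parametric test with assumed shifts, whereas the plan uses nonparametric randomization tests across time points with control for multiple comparisons.

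What does not stand is the claim of mere silence. The article commits to named contrasts at each EEG step, and those contrasts test change over time rather than difference in change. If a fuller plan includes group, the published text misdescribes it and still needs correcting.

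**Conclusion.** The point holds for the analysis as written. GFP, TANOVA and the sLORETA follow-up are specified by measurement time and stimulus type only, and such tests cannot separate an Alc-IT effect from retest, continuing abstinence, usual treatment or non-specific training. That conclusion is structural and needs no numerical assumption. The size of the resulting error does: 33% to 97% against about 5% depends on an assumed common shift of 0.2 to 0.5 SD, pooling of arms and a simple paired test, and serves only as an illustration.

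It would be tempting to treat this as a threat to the trial's main result. It is not. PDA, HDD and TFD at 3 months have their own analyses, and the EEG work is a mechanistic substudy of 60 of the 246 patients. The correction belongs before the EEG analysis, but the main conclusion does not depend on it.

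**What to change.** In Statistics, EEG substudy:

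- Name training group by measurement point as the test of the neurophysiological research question, for both GFP and TANOVA, with randomization of group labels across patients.
- Add the interaction with stimulus type, since the question concerns inhibition that is specific to alcohol.
- Report T2 versus T3 main effects as supportive only, not as evidence of an Alc-IT effect.
- Let sLORETA follow significant group by time effects.

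The cost is wording and one between-patient factor. No new data are needed, because all three versions are recorded at both time points. The downside is lower power than a before-after test: about 44% at n = 60 under the borrowed values, and not calculated here for the interaction with stimulus type. This should be stated openly. By the Trial status section data collection was still running, and the Statistics section defers the main training-effect analyses until it is complete, so the text can be corrected before the EEG results are examined.

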#### Cortisol substudy

Salivary cortisol concentrations are determined by a commercially available chemiluminescence immunoassay (CLIA; IBL, Hamburg, Germany). Inter- and intra-assay coefficients of variation are both below 8%. For biochemical analyses of free cortisol concentration, saliva samples will be thawed and spun at 3000 rpm for 10 min to obtain 0.5–1.0 ml of clear saliva with low viscosity.

### Power calculation

The intended sample size was calculated with G*Power (Version 3.1.5, Heinrich-Heine-University Duesseldorf, Dusseldorf, Germany). In a-priori analyses (1−β = 0.8, α = 0.05), slightly reduced expected effect sizes were entered compared to earlier studies because of the additional manipulations concerning different training versions and time of training. For the 2 × 3 ANOVA to examine the training effects on the primary outcome measures PDA and HDD (with an expected effect size of f = 0.2 based on earlier studies [32]), a total sample size of *n* = 244 is needed. For the analyses of the training’s effect on TFD (the third primary outcome, estimating a small to medium effect size of w = 0.25 based on earlier studies [37], and df = 3), G*Power indicated a total sample size of *n* = 174 for the Cox regression. For the 2 × 2 × 3 repeated measures ANOVA examining training effects on experimental parameters and also taking into account the effects of time of day of the training (expecting small to medium effects of f = 0.15 and correlations of 0.4 among repeated measures based on earlier studies [107]), the necessary sample size was *n* = 180. Considering the necessary power for all analyses and similar sample sizes in all study arms (82 per intervention group), a total of 246 patients will be recruited.

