## Background

Alcohol use disorder (AUD) is a major public health problem which has a substantial impact on patients’ psychological, physiological and social functioning [1–4]. Severe AUD often remains a lifelong condition due to patients’ susceptibility to relapse [5–7]. Despite the development of valuable treatment programs [8, 9], one third of patients relapse within 1 year after treatment, highlighting the need for effective new interventions to be added to these programs.

Current models of substance use disorders (SUDs) are based on neuroscientific research into subcortical alterations (e.g., [10–12]) and psychological investigations on implicit processes [13], and postulate on an imbalance between subcortical, implicit processes and cortical control processes. Briefly, these models assume that automated (subcortical) cue-reactivity is enhanced, thus leading to a strong drive to consume, while the opponent (cortical) executive control is weakened, making it difficult to inhibit this impulse (e.g., [11, 14–16]). The neuroscientific findings that underlie these models include enhanced reactivity to substance-related cues in brain regions related to reward prediction and saliency processing (e.g., nucleus accumbens, amygdala), habits and motivation (dorsal striatum, orbitofrontal cortex) and alterations in brain regions related to inhibitory control (dorsolateral prefrontal cortex, inferior frontal cortex and anterior cingulate cortex) [17, 18]. There is an extensive body of literature indicating that SUD is associated with impaired performance in inhibitory control tasks [19–24]. Until recently, these tasks did not differentiate between inhibition in a substance-related versus neutral context. However, this distinction seems to be clinically relevant, given that the central malfunction leading to relapse is the inability to exert inhibitory control in a substance-related context. Recent studies have suggested that alcohol-related inhibition demands additional neuronal resources in patients with AUD and heavy drinkers [25–28].

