#### Main study

Training effects on our primary outcome measures (PDA and HDD at 3-month follow-up) will be assessed with a 2 × 3 analysis of variance (ANOVA) with the factors time point (T1, T5) and training group (Alc-IT (50/50), Alc-IT (75/25) or control). Further, a Cox regression will be computed to predict the effect of the intervention on TFD (at 3-month follow-up).

Training effects on experimental test parameters will be assessed with a 2 × 2 × 3 repeated measures ANOVA with the factors measurement point (T2, T3), time of day (morning, afternoon) and training group (Alc-IT (50/50), Alc-IT (75/25) or control). Where Mauchly’s test of sphericity indicates heterogeneity of covariance, we will verify repeated measures results with Greenhouse-Geisser corrections.

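### The n = 174 given for the Cox regression is a generic 3-df chi-square count of patients with no event basis, so the stated 80% power for time to first drink is unsupported

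*Protocol article*

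**What the plan says.** In the protocol article, the section on Power calculation sets power at 0.8 and alpha at 0.05. For TFD it describes "estimating a small to medium effect size of w = 0.25 based on earlier studies [37], and df = 3", and reports that G*Power returned n = "174 for the Cox regression". The same sentence ranks TFD as "the third primary outcome, estimating a small to medium effect size".

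The analysis is fixed under Statistics, Main study: "a Cox regression will be computed to predict the effect of the intervention on TFD", at the 3-month follow-up. The factor described there for the other primary outcomes is "training group (Alc-IT (50/50), Alc-IT (75/25) or control", which has three levels. Time of day appears in that section only in the repeated measures ANOVA of the experimental tasks. No such term is named for the Cox model.

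The recruited number is justified by the power needed for all the analyses together, with "82 per intervention group), a total of 246 patients will be recruited". The largest single requirement is n = 244, for the ANOVA on percentage of days abstinent and heavy-drinking days.

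**The concern.** A Cox model draws its information from the number of first drinks observed, not from the number of patients enrolled. A sample size for it therefore needs an effect on the hazard scale and an expected number of events, or a share of patients with an event plus a censoring assumption. The section gives none of these. It gives an effect size w and a df, which are the inputs of a chi-square test.

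The df also looks out of line: three training groups give 2 df, not 3.

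TFD is a primary outcome. A reader who sees 174 needed and 246 recruited would take it as adequately powered, and might read a null TFD result as evidence against a small-to-medium effect. Whether that inference is safe depends on quantities the section does not state.

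**Working it through.** **Inputs.** Alpha 0.05, power 0.80, w = 0.25, df = 3 and n = 174 come from Power calculation. The three equal groups of 82 (246 in total) come from the same section. The Cox model on the intervention comes from Statistics, Main study. Shares with a first drink by 3 months are not given, so those below are assumptions shown as a range.

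**Step 1: reproduce 174.** Solve P(noncentral chi-square(df, lambda) > 95% critical value) = 0.80 for lambda, then n = lambda/w², with w² = 0.0625.

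| df | lambda | lambda/0.0625 | n, rounded up |
|---|---|---|---|
| 1 | 7.849 | 125.6 | 126 |
| 2 | 9.635 | 154.2 | 155 |
| 3 | 10.903 | 174.4 | 175 |
| 5 | 12.828 | 205.2 | 206 |

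Only df = 3 gives the stated figure; power at n = 174 is 79.9%. The count is of patients, and nothing about events enters it.

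**Step 2: df.** Three groups give 2 df, so the same inputs need 155. At 2 df, power on this chi-square basis is 84.8% at 174 and 94.9% at 246. The df slip alone therefore overstates the requirement by about 19 patients.

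**Step 3: w read per event (assumption).** Take lambda = D × w², where D is the number of first drinks and w is the standard deviation of the log hazard across the three equal arms. With 2 df, D = 9.635/0.0625 = 154.2, so 155 events, and 155/246 = 63%.

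If both Alc-IT arms share one effect, the variance of the log hazard across arms is (2/9)(log HR)². Setting this to 0.0625 gives |log HR| = 0.25 × √4.5 = 0.530, so HR ≈ 0.59. The HR detectable with 80% power is exp(−√(4.5 × 9.635/D)).

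| Share with a first drink (assumed) | Events in 246 | lambda = D × 0.0625 | Power at w = 0.25, 2 df | HR detectable at 80% power |
|---|---|---|---|---|
| 20% | 49 | 3.08 | 33% | 0.39 |
| 33% | 82 | 5.13 | 51% | 0.48 |
| 50% | 123 | 7.69 | 70% | 0.55 |
| 60% | 148 | 9.23 | 78% | 0.58 |
| 70% | 172 | 10.76 | 84% | 0.61 |

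**Step 4: w read as a drink-by-arm table (the alternative assumption).** Here patients are the right unit and the event share is already inside w. With equal Alc-IT arms and overall share p, w² = (2/9)δ²/(p(1−p)), where δ is control minus active. So δ = 0.25 × √(4.5 p(1−p)), control = p + 2δ/3, active = p − δ/3, and under proportional hazards HR = ln(1 − active)/ln(1 − control).

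| Overall share p (assumed) | δ | Control | Active | HR |
|---|---|---|---|---|
| 20% | 0.212 | 34.1% | 12.9% | 0.33 |
| 33% | 0.250 | 50.0% | 25.0% | 0.42 |
| 50% | 0.265 | 67.7% | 41.2% | 0.47 |
| 60% | 0.260 | 77.3% | 51.3% | 0.49 |

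On this reading 246 patients give about 95% power, but for an effect that at least halves the hazard over this range.

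**The case against.** Several points on the other side are sound.

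- **The sum is right.** The inputs do give 174 to rounding. The fault is that a chi-square count is labelled as a Cox sample size.
- **The df may be deliberate.** Power calculation says effect sizes were set with both training version and time of training in mind, and group (2 df) plus time of day (1 df) makes 3. But no time-of-day term is named for the Cox model, so this stays a possible explanation. Either way the slip is conservative.
- **174 does not set the sample size.** The ANOVA requirement of 244 does, rounded to three groups of 82. Removing 174 changes no recruitment. Even so, the article justifies 246 by the power for all analyses, so it does claim power for TFD.
- **"Small to medium" is a label on the scale of w.** Re-expressing w as a hazard ratio under added assumptions does not make that label an error.

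A reader might go further and infer that the trial can detect only very large TFD effects. Background states that "one third of patients relapse within" 1 year, and one third of 246 is 82. The documents do not support using 82 as a ceiling. The figure is general background on relapse after treatment, not a planning assumption. Relapse is not defined there as any first drink, and the drinking goals recorded include abstinence with occasional lapses and controlled drinking, so first drinks may outnumber relapses. Above a share of about 63%, the per-event reading reaches 80% power.

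**Conclusion.** The point holds in a limited form. The n = 174 is a generic 3-df chi-square patient count with no hazard ratio, event share or censoring behind it, so the 80% power stated for the Cox analysis of TFD is unsupported.

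How far actual power departs from 80% cannot be settled from the article. The per-event figures (33% to 84%) rest on an assumed mapping of w to log hazards, equal Alc-IT arms for the hazard ratios, and assumed first-drink shares of 20% to 70%. The table reading gives ample power, but only for hazard ratios of about 0.33 to 0.49. The article does not say which reading was meant. A conclusion that TFD is underpowered, or not sized for small-to-medium effects, would go beyond what is shown.

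The df mismatch is secondary and errs on the safe side. Severity is moderate: a stated figure for a primary outcome needs correcting, but the sample size and the conduct of the trial do not depend on it.

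**What to change.** Withdraw n = 174 as a sample size for the Cox regression. State the df of the Cox test actually planned: 2 if training group is the only term tested. If time of day is meant to be in the model, say so in Statistics, Main study.

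Then restate TFD power for the planned 246 patients as the detectable hazard ratio by number of first drinks at 3 months, over a stated range such as 20% to 70%. Mark the assumptions: event share, censoring, and how the effect is spread over the two Alc-IT arms. The table in step 3 can serve as a starting point.

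The cost is one corrected paragraph and a small table. No extra patients and no design change are needed. The article reports that data collection is still under way, so this can be done before the main analyses.

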#### Procedure to enhance response rates at the follow-up assessments (T5, T6, T7)

To achieve high response rates, a meticulous plan will be pursued for each follow-up assessment: Participants will be contacted by telephone starting 10 days prior to the target day (90, 180 and 365 days after discharge) to announce the upcoming assessment. Should three contact attempts fail, a text message is sent. In case of no response, they are called another seven times, and a set of questionnaires will be sent shortly before the target day. If these questionnaires are not returned within 15 days, they are called another 10 times. If provided, an additional email is sent. This procedure will be repeated if the patient has been reached yet no questionnaires are returned. If it is possible to talk to the participant at any time during the process, the most important primary outcome variables are queried. This entails that at least the most important variables can be collected, even if the participant does not return the questionnaires. As a last resort, a voluntarily provided contact of the participant is called. If none of these attempts succeed, the follow-up assessment will be terminated. Participants receive 20 CHF for each follow-up assessment.

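### For PDA and HDD the sample size leaves two patients for loss at 3 months, and the scale of f = 0.2 and the T1–T5 correlation are not given

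*Protocol article*

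**What the plan says.** The Power calculation section fixes the error rates first: "In a-priori analyses (1−β = 0.8, α = 0.05". The first calculation is a two-factor analysis of variance, whose purpose and effect size are given as "to examine the training effects on the primary outcome measures PDA and HDD (with an expected effect size of f = 0.2". It concludes that "a total sample size of *n* = 244 is needed". Two further calculations give 174 for time to first drink (TFD) and 180 for the experimental parameters. Recruitment is then set from the largest of the three: "similar sample sizes in all study arms (82 per intervention group), a total of 246 patients will be recruited".

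The Main study paragraph under Statistics describes the primary test for PDA and HDD as a "2 × 3 analysis of variance (ANOVA) with the factors time point (T1, T5) and training group". Time point is measured within patients and training group between patients.

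The section on enhancing follow-up response rates sets out repeated calls, a text message, an email and a call to a nominated contact. It ends: "If none of these attempts succeed, the follow-up assessment will be terminated".

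**The concern.** Two things stand out.

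1. The number stated as needed and the number to be recruited are almost equal, although the article expects some patients not to be reached at T5. The section moves directly from the analysable N to the recruited N. Both figures are in the article, so this is not a detail left to a fuller document.

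2. The article states a correlation between repeated measures (0.4) for the analysis of the experimental parameters, but none for the 2 × 3 ANOVA on PDA and HDD, which is also a repeated-measures design.

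PDA and HDD are primary outcomes, and 244 is the figure that sets the size of the whole trial. A null result would be read against the claimed 80% power, so a reader needs to know under what conditions that claim holds.

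**Working it through.** **Inputs from the article.** α = 0.05; power 0.80; f = 0.2; three groups; two time points; 244 needed; 246 recruited (3 × 82). **Assumed, because the article gives no figure:** loss at T5 of 5% to 30%, and the T1–T5 correlation r of PDA and HDD.

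**Step 1: reproduce 244.** Independent-groups ANOVA, noncentral F with λ = f²N, df1 = 2, df2 = N − k.
- N = 244: λ = 0.04 × 244 = 9.76; power 0.800 with k = 3 or k = 6. This is the smallest N that reaches 0.80.
- N = 246: λ = 9.84; power 0.804.

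The figure reproduces exactly.

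**Step 2: room for loss.** 246 − 244 = 2 patients, and 2/246 = 0.8%. With three lost, N = 243 and power is 0.798. Same formula at N = 246 × (1 − loss), rounded down:

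| Assumed loss at T5 | N analysed | Power |
|---|---|---|
| 0% | 246 | 0.804 |
| 5% | 233 | 0.780 |
| 10% | 221 | 0.757 |
| 20% | 196 | 0.701 |
| 30% | 172 | 0.639 |

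**Step 3: the other calculations.** TFD was sized at 174, which leaves 246 − 174 = 72 patients (29%). The experimental parameters were sized at 180, which leaves 66 (27%). Neither is tight in this way.

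**Step 4: the planned time × group test.** With two time points this test is a one-way ANOVA on the change score T5 − T1. Its power at N = 246 depends on what f = 0.2 is scaled by.

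- *(a) SD of the change score.* λ = f²N, as in Step 1. The required N is 244, and power at 246 is 0.80 with complete data. The losses in Step 2 apply unchanged.
- *(b) Repeated-measures convention with a stated correlation.* λ = f²N × 2/(1 − r). The required N is 124 at r = 0 and 76 at r = 0.4. Power at 246 is 0.983 at r = 0 and higher for r above 0. With 30% loss (N = 172) it is still 0.919 at r = 0.
- *(c) Group difference at T5 on the single-time-point SD, with equal baselines.* The change score has variance 2(1 − r) times the single-time-point variance, so λ = f²N/[2(1 − r)].

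| r in reading (c) | Power at N = 246 | N needed for 0.80 |
|---|---|---|
| 0 | 0.49 | 485 |
| 0.2 | 0.59 | 389 |
| 0.4 | 0.72 | 293 |
| 0.5 | 0.80 | 244 |

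No value of r from 0 to 0.7 gives 244 under (b).

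**Step 5: baseline adjustment under reading (c).** With the T1 value as covariate, residual variance falls by the factor 1 − r², so λ = f²N/(1 − r²) and one further error df is used. At r = 0.4:
- N = 246: λ = 9.84/0.84 = 11.71; power 0.87, against 0.72 for the planned interaction.
- N = 196 (20% loss): λ = 7.84/0.84 = 9.33; power 0.78, against 0.62.

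**The case against.** The strongest reply concerns the mismatch of tests. A reader might infer that 244 belongs to a different test and that the 80% is therefore false. The documents do not support that. Under reading (a), 244 is exactly right for the planned interaction. Under reading (b), 246 patients give at least 98% power and the missing loss allowance does no harm, so the two defects could offset each other. Only reading (c) with r below 0.5 lowers power at full retention. The article takes f from an earlier study and does not say which reading applies. This objection stands: the mismatch leaves the 80% unverified and does not show it to be wrong.

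Second, loss may be small. The follow-up procedure provides for asking the main outcomes whenever a patient is reached by telephone, even if no questionnaire comes back, and each follow-up is paid. At 5% loss the shortfall is only two percentage points. This is fair, and the larger rates above are assumptions. It does not restore the margin, because the third lost patient uses it up under the plan's own calculation.

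Third, the article does not say how missing T5 values are handled, and an analysis plan that is not shown may do so. Dropping patients without T5 is what a T1–T5 ANOVA does as ordinarily run; it is not a stated rule. The absence of a missing-data method is therefore no part of this point.

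Fourth, the correlation of 0.4 belongs to the experimental tasks. Nothing in the article supports it for drinking outcomes, so the 0.72 and 0.87 figures illustrate one case only.

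**Conclusion.** The point holds for PDA and HDD only. No arithmetic is wrong: 244 reproduces, and 3 × 82 = 246. On the plan's own calculation, however, 80% power needs near-complete T5 data. It is lost with the third missing patient and is about 0.78, 0.76, 0.70 and 0.64 at an assumed 5%, 10%, 20% and 30% loss.

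Separately, the 80% cannot be checked against the planned time × group test. Depending on the meaning of f = 0.2, power at N = 246 with full data is 0.80 (change-score scale), 0.98 or more (repeated-measures convention), or 0.49 to 0.80 for r from 0 to 0.5 (single-time-point difference at T5). The article does not settle which applies, so the direction of any error is open.

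**What to change.** No extra enrolment is needed.

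- In the power paragraph, state what f = 0.2 is scaled by and the T1–T5 correlation assumed for PDA and HDD.
- Restate power, or the detectable f, for these two outcomes at the analysable N over a stated range of T5 loss. Leave the TFD and experimental-parameter calculations as they are.
- Analyse T5 PDA and HDD with adjustment for the T1 value already collected, in a likelihood-based model or with multiple imputation, so that patients without T5 are not simply deleted. If f = 0.2 is the T5 difference and r = 0.4, adjustment more than offsets the shortfall at full retention and nearly does so at 20% loss (Step 5).

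The cost is a rewritten paragraph and a change of primary model, to be fixed before unblinding; the article reports that data collection was still under way. The downside is that the stated power may become slightly less favourable.
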